## Abstract

**Background:**

Patellofemoral pain is one of the most frequent knee conditions among adolescents with a prevalence of 7 %. Evidence-based treatment consists of patient education combined with hip and quadriceps strengthening. Recent evidence suggests that a large proportion of adolescents does not follow their exercise prescription, performing too few repetitions or too fast below the prescribed time under tension. Live feedback, such as a metronome or exercise games, has previously shown promising results in improving the quality of exercises. The aim of this study is to investigate if live feedback from a sensor (BandCizer™) and an iPad will improve the ability of adolescents with PFP to perform exercises as prescribed.

**Methods:**

This study is a randomized, controlled, participant-blinded, superiority trial with a 2-group parallel design. Forty 15 to 19 year old adolescents with patellofemoral pain will be randomized to receive either live visual and auditory feedback on time under tension or no feedback on time under tension during a 6-week intervention period. Adolescents will be instructed to perform three elastic band exercises. Feedback will be provided by BandCizer™ and an iPad. The adolescents perform the exercises twice a week unsupervised and once a week during a supervised group training session. The primary outcome will be the mean deviation of the prescribed time under tension per repetition in seconds during the course of the intervention.

**Discussion:**

Low compliance is a major problem among adolescents with patellofemoral pain. Providing the adolescents with real time feedback on time under tension from a sensor and an iPad could potentially help the adolescents perform the exercises as prescribed. This may increase the total exercise dosage they receive during treatment which may help improve patient outcomes.

**Trial registration:**

Registered at ClinicalTrials.gov (identifier: NCT02674841) on February 4^th^ 2016.

## Background

Thirty percent of adolescents between 15 and 19 years old report having knee pain [1]. Patellofemoral Pain (PFP) is one of the most frequent knee conditions among adolescents and has a prevalence of 7 % [2, 3]. Patients usually describe their pain as being diffuse anterior knee pain that is aggravated by sitting for prolonged periods, climbing or descending stairs, running or squatting [2].

Evidence-based treatment of PFP consists of patient education combined with hip and quadriceps strengthening [2, 4]. A meta-analysis based on studies of PFP in adults reported a positive effect of multimodal treatment with 62-84 % being fully recovered 12 months after the treatment [5]. The latest review on PFP in adolescence and adulthood indicates that treatment seems to have a somewhat lower effect in adolescence [6]. The reason for this is unknown, but compliance seems to play an important role [7].

Hip and quadriceps exercises have a better effect if the exercises are performed more frequently [7, 8], however a large proportion of adolescents do not follow their exercise prescription [7] or they perform the exercise too fast with too few repetitions thus not performing the prescribed exercise dose (Rathleff et al. *in review*). Exercise parameters such as load, time under tension (TUT), range of motion (ROM), the number of repetitions and sets being performed collectively influence the total exercise dosage patients receive during rehabilitation [9]. The question is if live feedback during exercises may improve compliance by helping adolescents perform the exercise as prescribed and, thus, helps them achieve the prescribed exercise dosage.

Previous research has shown promising results in various populations when using a metronome for guidance [10, 11] or exercise games as live feedback [12] and thereby improving the quality of exercises. Some shortfalls of these strategies are that a metronome does not give feedback on the exercises performed and exercise games often require a lot of space in order to be able to capture the user performing the exercises by camera.

One way to provide adolescents with live feedback on the quality of home-based elastic band exercises is by using a sensor called BandCizer™ (BandCizer Aps, Denmark). A systematic review on self-reported compliance by Bollen et al. identified a need for a valid instrument that can measure compliance to prescribed home-based exercises [13]. Pertaining to this need, BandCizer™ is a valid tool that can quantify compliance and measure the number of repetitions performed, TUT and the force used to stretch the elastic band (pulling force). BandCizer™ consists of two parts that are mounted on either side and held together by internal magnets. It transmits data to an iPad with the BandCizer™-app [14, 15]. The app can supply the user with live feedback on TUT and pulling force. This exercise-integrated system may thus help the adolescents with PFP to perform the exercises as instructed.

### Purpose

The purpose of this study is to investigate if live feedback on TUT during home-based exercises will improve the ability to perform the exercises with the prescribed TUT per repetition compared with no feedback on TUT among adolescents with PFP during a 6-week intervention.

### Hypothesis

Hypothesis: adolescents who receive live feedback on TUT from BandCizer™ (feedback group) will have a significantly lower mean deviation from the prescribed TUT compared to the group not receiving feedback on TUT (controls) during the course of the intervention.

## Methods

### Study design

This study, which is called the The XRCISE-AS-INSTRUcted-1 trial, is a randomized, controlled, participant-blinded, superiority trial, with a 2-group parallel design to be conducted in Aalborg, Denmark. The primary endpoint will be 6 weeks after an initial exercise instruction, using a summary of exercise dosage-data collected from 0 to 6 weeks. Reporting of this study will follow CONSORT guidelines for reporting parallel group randomized trials with the extension for non-pharmacological treatments and TIDieR for intervention description [16, 17]. Reporting of this protocol will follow the SPIRIT statement [18]. The study will be conducted at the Department of Occupational Therapy and Physiotherapy at Aalborg University Hospital in Denmark.

### Intervention

Once informed consent has been gained, the participants will be instructed in performing three exercises with an elastic band; knee extension (Fig. 1), hip abduction (Fig. 2) and hip extension (Fig. 3). These types of exercises have previously been tested and found effective in patients with PFP [2, 19, 20]. The exercise descriptors, which are adopted from the mechano-biological descriptors from Toigo and Boutellier [21], are described in the table below (Table 1).

**Fig. 1 Fig1:**
[figure not shown]
Knee extension. The subject provided consent to appear

**Fig. 2 Fig2:**
[figure not shown]
Hip abduction. The subject provided consent to appear

**Fig. 3 Fig3:**
[figure not shown]
Hip extension. The subject provided consent to appear

**Table 1 Tab1:** Exercise descriptors

	Knee extension (Fig. 1)	Hip abduction (Fig. 2)	Hip extension (Fig. 3)
1. Load magnitude	10-12 RM	10-12 RM	10-12 RM
2. Number of repetitions	10	10	10
3. Number of sets	3	3	3
4. Rest in between sets	1 min 50 seconds	1 min 50 seconds	1 min 50 seconds
5. Number of exercise interventions (per (day) or week)	3/week	3/week	3/week
6. Duration of the experimental period ((day) or weeks)	6 weeks	6 weeks	6 weeks
7. Fractional and temporal distribution of the contraction modes per repetition and duration (s) of one repetition	3 s concentric	3 s concentric	3 s concentric
	2 s isometric	2 s isometric	2 s isometric
	3 s eccentric	3 s eccentric	3 s eccentric
8. Rest in-between repetitions ((s) or (min))	No	No	No
9. TUT ((s) or (min))	8 s/repetition	8 s/repetition	8 s/repetition
	80s/set	80s/set	80s/set
	4320 s/total intervention	4320 s/total intervention	4320 s/total intervention
10. Volitional muscular failure	Yes	Yes	Yes
11. Range of motion	90° to 180^o^	0° to 45^o^	45° hip flexion to 0° hip flexion/extension
12. Recovery time in-between exercise sessions ((h) or (d))	48 h	48 h	48 h
13. Anatomical definition of the exercise (exercise form)	Knee extension is performed with the participant sitting in 90^0^ knee flexion. The elastic band is looped around the ankle and around a solid anchor near the floor under the participant (Fig. 1). The knee is extended to approximately 180^0^.	Hip abduction will be performed in standing with the elastic band looped around the ankle and anchored to the wall at ankle height. The stance leg will be in front of the band and the target hip in a slight internal rotation (Fig. 2). Hip abduction will then be performed to approximately 45^0^.	Hip extension will be performed in standing with target hip in 45^0^ hip flexion. One end of the elastic band fixated at knee height and looped around the back of the knee (Fig. 3). The hip is then extended to approximately 0° hip extension whilst maintaining a neutral lumbo-pelvic position.

Participants will receive an elastic band, a BandCizer™ and an iPad with the BandCizer™-app. Before and after each exercise they are instructed to record their knee pain on a 100 mm VAS that is integrated in the app. They are instructed to perform the exercises three times each week during the 6-week intervention. Twice a week the exercises are performed at home whilst the last exercise session will be a group training session supervised by a physiotherapist. In connection with the initial instruction of the exercises, 10-12 RM will be determined by shortening the elastic band to a length where the participants feel that they will not be able to perform more than 10 repetitions. The pulling force exerted when the exercise is performed correctly will be measured by the BandCizer™ and recorded by the investigator. If the participants become able to perform more than 10 repetitions during the intervention period, they will be instructed to shorten the band or change to a different grade of band. In this situation a new measurement of recommended pulling force will be made.

The feedback group will have access to live visual and auditory feedback on TUT and pulling force from the BandCizer™-app when they perform the exercises. Controls will only receive visual feedback on pulling force.

### Withdrawal and adverse events

If a participant experiences an adverse event (e.g. an injury to the musculoskeletal system such as a muscle tear, a muscle strain, a sprained joint, injury from falling, DOMS that lasts for more than 48 h after performing the exercises or exacerbation of PFP) and is not able to perform the exercises, the participant will be able to withdraw from the study. The study may also be discontinued by participant request or withdrawal of informed consent. Data until the point of withdrawal will be included in the data analyses. If a participant experiences an adverse event and has to withdraw, data until the last training before the adverse event occurred will be included in the analyses. The participants are instructed to report any adverse events to the primary investigator as quickly as possible either by e-mail, SMS, phone call or during the supervised training sessions. The primary investigator will then ask the participant if the event occurred when they performed the exercises or during other activities. If the event occurred during the exercises the primary investigator will report the incident to the sponsor as quickly as possible and no later than 15 days after the participant reported the event. Sponsor will report adverse events to the Ethics Committee of North Denmark Region no later than 7 days after being informed.

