Secondary outcomes:The total number of repetitions performed during the intervention period.Pulling force exerted per repetition measured in kilos. This will be expressed as the maximum pulling force during each repetition and corresponds to the resistance used when calculating training volume [26].Isometric strength (presented as Nm/kg) of knee extension, hip extension and hip abduction. Isometric strength will be collected at baseline and follow-up and will be used to explore the association between total exercise dose and changes in isometric strength. Isometric strength will be recorded at baseline and post intervention using a dynamometer (Commander PowerTrack, JTECH Medical, Midvale, Utah, USA) and will follow the protocol by Rathleff et al. [27] for knee extension (ICC= > 0.92). The test for hip abduction and hip extension will follow the test positions of the side-lying hip abduction (ICC = 0.76) and the hip extension with a short lever (ICC = 0.81) described by Thorborg et al. [28].Pain measured on a 100 mm VAS, where 0 mm is no pain and 100 mm is worst pain imaginable. The participants will enter their rating of pain intensity into the BandCizer™-app before and after each exercise. Pain is chosen as an outcome measure to investigate if the participants are more likely to comply to exercises that cause less pain.Kujala Patellofemoral Scale-score (0-100 score, with 0 as complete disability and 100 as fully functional). The Kujala Patellofemoral Scale is a frequently used validated outcome measure in PFP [19, 29, 30] however, it does not come in a Danish version. Therefore a Danish translation has been made with the same content and wordings as the original English version and a backwards translation to English was made according to principles of the translation of patient-reported outcome measures [31], however the translation has not been published. Kujala will be collected at baseline and at follow-up.Global rating of change at follow-up. This will be used to measure the participants’ self-reported recovery on a 7-point Likert scale ranging from “much improved” to “much worse”. Participants are categorised as improved if they rate themselves as “much improved” or “improved” (category 6-7) and categorised as not improved if they rate themselves from “slightly improved” to “much worse” (category 1-5). A 7-point Likert scale to assess self-reported change from baseline has previously been used in studies resembling this study [7, 19].

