### Analysis population and missing data

Participant data will be analysed on an intention-to-treat (ITT) basis as per group allocation. Any missing repetitions from the prescribed number of repetitions will be interpreted as non-compliance. Mean values of data until the point of drop out will be imputed for the remaining intervention for participants who drop out. If the participant has not made a single repetition, the group mean value will be imputed for this participant.

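### Read literally, the data cut-off for adverse-event withdrawals excludes their observed 6-week clinical outcomes, which conflicts with the intention-to-treat statement; it should be limited to session data

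*Protocol article*

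**What the plan says.** The section Withdrawal and adverse events sets two cut-offs. The general one is that "Data until the point of withdrawal will be included in the data analyses". The second applies when a participant has an adverse event and has to withdraw; then "data until the last training before the adverse event occurred will be included in the analyses". The examples of adverse events include "DOMS that lasts for more than 48 h after performing the exercises or exacerbation of PFP". Withdrawal is optional: someone who has an event and "is not able to perform the exercises, the participant will be able to withdraw from the study".

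The Outcomes section fixes when the clinical outcomes are measured. Kujala score and isometric strength are taken at baseline and at follow-up. The global rating exists once: "Global rating of change at follow-up. This will be used to measure the participants’ self-reported recovery". Pain is entered in the app around each exercise, so it has values before any event. All of these are secondary outcomes.

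The section Analysis population and missing data states that "Participant data will be analysed on an intention-to-treat (ITT) basis as per group allocation". For those who leave, "Mean values of data until the point of drop out will be imputed for the remaining intervention for participants who drop out", and a participant with no repetitions at all receives the group mean. The Statistical analysis section compares the groups by *t*-test for Kujala and strength and by relative risk for the dichotomised global rating.

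**The concern.** The stricter of the two cut-offs falls on people who withdrew because something went wrong, and a worse knee is one of the listed reasons. For sensor data this is understandable, because a session disturbed by an injury says little about whether feedback helps someone keep to the prescribed time under tension. For outcomes measured once, at six weeks, the same sentence removes the only post-baseline value.

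Two things are at stake. First, excluding an observed outcome because of an event after randomisation is not analysis by allocation. Second, the exclusion is related to the outcome, since worsening can lead to withdrawal and withdrawal to loss of the value that would show the worsening.

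A difference between arms is plausible but not shown. The sample size section expects about 8 s per repetition with feedback and 6.5 s without, and 8/6.5 = 1.23, or about 23% more time under tension per repetition in the feedback arm.

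**Working it through.** The plan gives no figure for this point, so the check starts with the text and then adds an illustration on stated assumptions.

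**Step 1: what the cut-off leaves for an adverse-event withdrawer, read literally**

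| Outcome | When measured | Left before the cut-off | What the imputation rule supplies |
|---|---|---|---|
| Time under tension, repetitions, pulling force | each session | sessions before the event | own mean before drop-out |
| Pain (app) | around each exercise | ratings before the event | own mean before drop-out |
| Kujala, isometric strength | baseline, follow-up | baseline only | at best the baseline value, i.e. no change |
| Global rating of change | follow-up only | nothing | nothing of the participant's own |

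The imputation rule is written for the remainder of the intervention period and refers to repetitions. It works for the first row. For Kujala and strength it would record a worsened participant as unchanged. For the global rating there is no earlier value to average.

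**Step 2: how many participants could be involved**

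No adverse-event rate and no drop-out rate is stated. The sample size section needs 15 per group, so 2 × 15 = 30, and enrols 40. The implied allowance is (40 − 30)/40 = 25%, or 5 per arm of 20. This covers drop-out for any reason, so it serves only as an upper end for the illustration.

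**Step 3: effect on the relative risk (assumed)**

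Assumptions: 20 per arm; the same number x improved in each arm; k participants, all not improved, lost from one arm only; complete cases analysed.

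- True RR = (x/20)/(x/20) = 1.00
- RR after the loss = (x/(20 − k))/(x/20) = 20/(20 − k), whatever x is

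| k | 1 | 2 | 3 | 4 | 5 |
|---|---|---|---|---|---|
| RR | 1.05 | 1.11 | 1.18 | 1.25 | 1.33 |

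The shift favours the arm with the losses.

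**Step 4: effect on Kujala (assumed)**

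If k of 20 participants in an arm truly fall by D points and baseline is used instead, that arm's mean is too favourable by k × D/20. For D = 10 this is 0.5 points (k = 1) to 2.5 points (k = 5). For D = 20 it is 1.0 to 5.0 points.

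**Step 5: when there is no bias between groups**

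If k and D are the same in both arms, the Kujala errors cancel. With equal k and equal x, the RR stays at 1.00, because (x/(20 − k))/(x/(20 − k)) = 1. Bias needs a difference by arm in the withdrawals or in the worsening among those who withdraw.

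**The case against.** The strongest objection is about reach. The cut-off is expressed in training sessions, and the section never mentions Kujala, strength or the global rating. It was probably written for sensor data. This stands as a reading of intent, but the sentence refers to data without restriction, so an analyst following it literally would exclude a 6-week value already in hand. If session data were meant, saying so settles that part.

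A reader might infer that everyone whose knee got worse drops out of the clinical comparison. The protocol does not support that. The rule needs both an adverse event and withdrawal, withdrawal is optional, and those who worsen and continue provide their follow-up as planned. The Compliance and participant retention section also contacts people who miss sessions and asks them to return.

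A reader might also treat a distorted relative risk as the plan's own result. It is not. The plan sets no complete-case denominator and assigns participants to their allocated group, so the figures above depend on the assumed one-sided losses and on complete-case analysis. They are also small beside sampling error: with 9 of 17 against 9 of 20 improved (k = 3, x = 9), the RR of 1.18 has a 95% confidence interval of about 0.61 to 2.28. The Monitoring section reports no adverse effects from earlier use of this exercise intervention, which suggests low numbers.

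Nor does it follow that harm would go unseen. Participants report adverse events to the primary investigator, and events during the exercises go on to the sponsor and the ethics committee.

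Finally, the analysis plan and the assessment schedule (Table 2) are not shown and may say more about follow-up after withdrawal. That is a reason not to criticise silence. It does not remove a rule that the article states, and no analysis plan can recover outcomes that were never collected.

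**Conclusion.** The point holds in a limited form. For participants who withdraw because of an adverse event, the stated cut-off, read literally, rules out any observed 6-week Kujala, strength or global rating. The imputation rule offers only baseline for the first two and nothing of the participant's own for the third. This conflicts with the intention-to-treat statement and makes the loss depend on the outcome.

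The consequence is modest. Only secondary outcomes are affected in this way; the primary outcome comes from session data, for which the cut-off and the imputation rule are workable. The direction and size of any bias cannot be known from the document. The range of 1.05 to 1.33 for a true relative risk of 1.00 rests on 20 per arm, 1 to 5 non-improved losses in one arm only, and complete-case analysis. With equal losses and equal worsening the bias is about zero. The change is worth making because it is cheap and must be made before follow-up is missed.

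**What to change.** - State that the adverse-event cut-off applies only to exercise-session data: time under tension, repetitions, pulling force and app-recorded pain.
- Separate stopping the exercises from withdrawing from the study. This concerns data collection only and leaves the clinical decision to stop as it is.
- Invite every randomised participant who has not withdrawn consent to the scheduled 6-week assessment. Kujala and global rating can be taken by phone or form if needed, and strength where feasible.
- Analyse these outcomes by allocation, and align the wording of the withdrawal section with Analysis population and missing data.

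The cost is about one paragraph of protocol text and a few extra follow-up contacts around an assessment already planned. Some participants who stopped will decline, so some missing data will remain.

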**Fig. 5 Fig5:**
[figure not shown]
BandCizer-app without feedback on TUT

All group training sessions will be planned before the intervention starts for all participants. If they are unable to attend any of the sessions, they are asked to contact the primary investigator by phone or e-mail and they will then be instructed to do the exercises at home instead. If any participant fails to show up for a training session and did not cancel beforehand they will be contacted by the primary investigator and asked in a friendly manner if they will return to the next group training session and they will be asked to do the missing training session at home.

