### Strengths

The recruitment and study design has several strengths. Firstly, the use of BandCizer™ provides an objective measure of compliance which was requested in the latest systematic review on self-reported compliance to home-based exercise programs [13]. A recent study showed that adolescents reported a 2.3 times higher exercise dosage in their exercise diary compared to TUT data from the BandCizer™ (Rathleff et al. *in review*)*.* This highlights the importance of an objective measure of compliance. Secondly, the participant blinding of primary outcome measures will ensure that the participants do not focus more on performing the exercises as prescribed than they would when receiving standard exercise prescription by a physiotherapist. Thirdly, the inclusion criteria used in this study are in line with those of previous studies of this patient group [3, 7, 29, 34] which will make comparisons across studies easier. Fourthly, reporting the study protocol using the SPIRIT statement, and outlining the specific exercise descriptors, which has been requested in a recent review on exercise interventions for patients with chronic conditions by Hoffmann et al. [37], facilitates the replication of the study’s findings and its translation into clinical practice. Fifthly, the intervention resembles current physiotherapy practice by combining home-based and supervised training sessions, which increases the external validity.

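### Adverse events are recorded by a participant-initiated route, and the planned contacts are not stated to include an enquiry, so events may be under-recorded and some withdrawals misclassified (minor)

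*Protocol article*

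**What the plan says.** The section *Withdrawal and adverse events* of the protocol article sets out the route in sequence.

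- Reporting starts with the participant: "The participants are instructed to report any adverse events to the primary investigator as quickly as possible". The channels are e-mail, SMS, telephone or the supervised sessions.
- The investigator's question comes next: "The primary investigator will then ask the participant if the event occurred when they performed the exercises or during other activities".
- Events that occurred during the exercises then go to the sponsor and on to the ethics committee, within stated time limits.
- The examples of events include muscle tears, strains, sprains, fall injuries, and "DOMS that lasts for more than 48 h after performing the exercises or exacerbation of PFP".
- If an adverse event forces withdrawal, "data until the last training before the adverse event occurred will be included in the analyses". For other withdrawals, data up to the point of withdrawal are kept.

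Planned contacts appear elsewhere.

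- *Intervention* (text after Table 1): "Twice a week the exercises are performed at home whilst the last exercise session will be a group training session supervised by a physiotherapist".
- *Compliance and participant retention*: a participant who cancels a group session contacts the investigator and trains at home. One who is absent without notice is contacted, "asked in a friendly manner if they will return to the next group training session", and asked to make up the session at home.
- *Outcomes*: strength, Kujala score and global rating of change are collected at follow-up. Pain is rated in the app before and after each exercise, for the stated purpose of relating pain to compliance.

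*Monitoring* provides for no data monitoring committee and no stopping rules.

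**The concern.** How events are found is a matter of data collection. An analysis plan can tabulate what was recorded, but it cannot recover an event that nobody asked about. The article is not silent here. It describes a sequence in which staff ask something only after the participant has spoken. Supervised sessions are named as a place where a participant may report, not as a point at which staff enquire.

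Two things are at stake. The first is the safety record of the trial, which rests on this route because there is no monitoring committee. The second is the primary dataset. The reason for a withdrawal decides where that participant's data end, so an event that was never mentioned can change which repetitions enter the primary outcome.

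**Working it through.** **1. Stated contacts and stated enquiries.** The documents give no adverse-event rate or other safety figure to reproduce, so the sections are set side by side.

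| Contact | Stated content | Adverse-event enquiry stated? |
|---|---|---|
| Weekly supervised session (1 × 6 weeks = 6 planned) | Training; participants may report events | No |
| Contact after unannounced absence | Return to next session; make up the missed one | No |
| Contact when a session is cancelled | Train at home instead | No |
| 6-week follow-up | Strength, Kujala, global rating of change | No |
| App, before and after each exercise | Knee pain VAS | No; used for pain and compliance |

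The pain rating is frequent: 3 exercises × 18 sessions × 2 = 108 ratings per participant at full compliance. It bears on exacerbation of patellofemoral pain. A knee pain score does not identify a strain elsewhere, a fall or prolonged muscle soreness.

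**2. Scale of under-recording.** Expected participants recorded with an event in an arm of 20 = 20 × event rate × share captured. All rates and shares are assumptions.

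| Event rate | 100% captured | 75% | 50% | 25% |
|---|---|---|---|---|
| 10% | 2 | 1.5 | 1 | 0.5 |
| 30% | 6 | 4.5 | 3 | 1.5 |
| 50% | 10 | 7.5 | 5 | 2.5 |

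**3. Effect on the primary data.** *Withdrawal and adverse events* ends data at the last training before the event for an adverse-event withdrawal, and at the point of withdrawal otherwise. *Analysis population and missing data* then fills the remaining period with the participant's mean up to drop-out. If the event is never mentioned, any sessions between event and withdrawal stay in, and they also enter the imputed mean.

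Let f be the share of the retained sessions that fall after the event (f < 1), and let d be the change in mean deviation after the event. That participant's value shifts by f × d, and the mean of an arm of 20 shifts by f × d / 20. Taking d as 1.5 s (an assumption, equal to the planned difference of 8 − 6.5 s), the shift is below 1.5 / 20 = 0.075 s per misclassified participant, or under 5% of the planned difference.

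**4. What a comparison by arm could show.** Fisher's exact test at 20 per arm (two-sided 5%) has power of 24% for 30% v 10% and 41% for 50% v 20% (assumed rates). With 0 of 20 recorded, the exact one-sided 95% upper limit is 1 − 0.05^(1/20) = 13.9%. That limit applies to the true event rate only if capture is complete. At 50% capture (assumption) it becomes 0.139 / 0.5 = 27.8%.

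**The case against.** The strongest reply is that the absence of a question cannot be proved. The assessment schedule (Table 2) is a figure that is not shown, and an article condenses the full protocol, where the wording of such a question could sit. This stands in part. The point can only be that the visible text describes participant-initiated reporting and states no enquiry. It remains worth making because the article gives the route step by step and puts the investigator's question after the report.

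It is also fair that harm would not go wholly unseen. Pain is prompted in both arms, the global rating extends to much worse, analgesic use is registered, and an absent participant is contacted by the same investigator who receives reports. These reduce the gap without closing it.

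Several stronger readings are tempting and are not supported.

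- *Events are not compared between arms.* No such comparison is listed under *Statistical analysis*, but that section refers to a separate analysis plan that is not shown, and such tables commonly sit there.
- *The article itself shows that adolescents report events unreliably.* The passage under *Strengths*, "adolescents reported a 2.3 times higher exercise dosage in their exercise diary", concerns over-reported exercise dose. It says nothing about unreported injuries.
- *Injury is most likely among absentees.* This may be plausible, but nothing in the documents shows it.
- *Capture differs by arm.* Both arms get the same instruction and channels. Separate training sessions make unequal informal prompting possible, but the plan does not build it in.
- *No recorded events would be an easy outcome.* With a 20% event rate and half captured (assumptions), one arm records none with probability 0.9^20 = 12.2%, against 0.8^20 = 1.2% with full capture. For all 40 participants it is 0.9^40 = 1.5%.
- *Every participant is seen weekly.* Weekly contact is planned, but cancelled or missed sessions are done at home.

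**Conclusion.** The point holds as a minor one. The described route depends on the participant speaking first, and no enquiry is stated at the supervised sessions, the contact after an absence or the follow-up. Under-recording is therefore possible. Its extent is unknown, because the documents give neither an event rate nor a capture rate. Under the assumed ranges, recorded counts per arm fall in proportion to capture, for example from 6 to 3 at a 30% event rate and half captured.

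Misclassified withdrawals could alter which repetitions are analysed. The effect is below 0.075 s on an arm mean per such participant, provided that performance changes by no more than 1.5 s after the event. This does not threaten the primary conclusion. The case for acting is that the remedy is nearly free and that unasked events are hard to recover later.

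**What to change.** Add to *Withdrawal and adverse events* that every participant in both arms is asked the same fixed question about the listed events since last contact, at three points:

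- each supervised session;
- the contact after a missed or cancelled session, by phone or message;
- the 6-week follow-up.

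Record the answer whether or not an event is reported, so that the reason for any later withdrawal can be classified. Report the number of participants with at least one event by arm, with confidence intervals, as description only. If the full protocol or the analysis plan already contains the question or the table, a sentence saying so is enough.

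The cost is one question at contacts that largely take place already, an occasional message, and one table. More minor events will be recorded, and at 20 per arm the counts cannot support a formal comparison. Sample size, endpoint and primary analysis are unchanged.
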